### Secondary outcomes

#### Bristol Stool Form Scale (BSFS)

Stool consistency will be evaluated using BSFS, a standardized scale that classifies stool consistency into seven categories [24]. Types I and II signify constipation; whereas types III and IV are regarded as the optimal stool shapes, with type IV being the easiest to pass. Types V to VII indicate the potential for diarrhea.

#### Quality of life

The Patient Assessment of Constipation-Quality of Life (PAC-QoL) [25] and the Fecal Incontinence Quality of Life (FI-QoL) instruments are employed to evaluate the quality of life of participants [26]. The PAC-QoL questionnaire consists of four domains: physical discomfort, satisfaction, psychosocial discomfort, and worries and concerns, featuring a total of 28 items. Each item is rated on a 5-point scale (0–4), where higher scores signify a lower quality of life. Meanwhile, the FI-QoL questionnaire is composed of four sections, encompassing a total of 27 questions that assess lifestyle (9 questions), behavior (8 questions), emotion (7 questions), and embarrassment (3 questions). Item scores range from 0 to 4.

#### Sample size

The sample size calculation was performed using the PASS15 software, Version 15.0.5, with reference to a prior randomized controlled trial conducted in China that reported the Wexner score as the primary outcome [27]. We selected a significance level of 0.05 and a power of 90%. Assumptions encompassed an equal allocation of participants in a 1:1 ratio between two groups and a 20% dropout rate. The mean for group 1 (μ_1_) was 10.65, and group 2 (μ_2_) was 9.10. The standard deviation for group 1 (σ_1_) was 2.08, and for group 2 (σ2), it was 1.73. The anticipated effect size was 0.81. The sample size calculation indicated that each group should comprise 40 patients.

## Assignment of interventions

### Allocation—sequence generation

Participants will first be stratified into two groups based on their baseline National Institutes of Health Stroke Scale (NIHSS) scores: one group with scores ranging from 0 to 4 and the other group with scores ranging from 5 to 15. Participants will then randomly be assigned in a 1:1 ratio to either the intervention or control arm. Random numbers within the range of 0 to 1 will be generated using the SPSS 25.0 software by an independent statistician and subsequently ranked. The allocation of participants will be determined based on the ranking of the generated random numbers. For the group with NHISS scores ranging from 0 to 4, odd-ranked numbers will be allocated to the intervention group, while even-ranked numbers will be assigned to the control group. Conversely, in the range of 5 to 15, this allocation will be reversed.

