### Statistical analyses

The collected data will undergo analysis using IBM SPSS Statistics 25.0 (IBM Corp., Armonk, NY, USA). Baseline characteristics will be summarized using descriptive statistics. Continuous variables, such as the Wexner score and quality of life score, will be reported using means, medians, standard deviations, and score ranges. Categorical valuable, such as BSFS, will be reported as counts and percentages. To ascertain normality, the Kolmogorov-Smirnova test will be applied. In instances of normally distributed data, independent samples *t*-test will be employed to compare efficacy between the intervention and control groups in terms of the Wexner score, PAC-QoL, and FI-QoL. Non-normally distributed data will be analyzed using the Wilcoxon rank sum test with a test statistic of *Z*. For assessing changes across distinct time points, we will employ repeated measures ANOVA. The chi-squared test will be used to analyze categorical data for the BSFS. A *p*-value < 0.05 will be considered statistically significant. We will perform an intention to treat analysis for participants who either lack adherence to bowel care (defined as comply with less than 80% of bowel care) or discontinue the study. These participants will be retained within their originally randomized treatment arm for analysis. Addressing missing data, a multiple imputation method will be implemented. No supplementary analyses will be carried out in this study, and the study design does not encompass interim analyses.

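### The primary Wexner comparison ignores the NIHSS stratification factor and the baseline score, so it is conservative and gives up a little power that could be had at no cost

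*Protocol article*

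**What the plan says.** Under Allocation—sequence generation, the protocol article divides participants by baseline NIHSS into 0–4 and 5–15 and randomises 1:1 within each stratum. Random numbers are generated and ranked. In the lower stratum, "odd-ranked numbers will be allocated to the intervention group, while even-ranked numbers will be assigned to the control group"; in the upper stratum the rule is reversed. No block size or list length is given. Under Allocation—concealment mechanism, each patient opens a sealed envelope after consenting, so the lists are used up as patients arrive.

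Under Statistical analyses, an independent-samples t-test "will be employed to compare efficacy between the intervention and control groups in terms of the Wexner score" and the two quality-of-life scales, with a Wilcoxon rank sum test if normality fails. Change over time is to be examined by repeated measures ANOVA. None of these is described as including the NIHSS stratum or a baseline value. The section closes by stating that there will be no supplementary analyses.

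**The concern.** A stratified design makes the arms alike on the stratification factor. If that factor predicts the outcome, the treatment difference varies less from trial to trial than it would without stratification. An unadjusted t-test does not know this. It leaves the between-stratum variation in its error term, so its standard error is too large and it rejects less often than its nominal level allows.

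Where stratification leaves some imbalance by chance, the unadjusted difference carries it and nothing in the plan removes it. A model containing the stratum deals with both situations.

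At stake is a modest amount of precision in a trial of 80 patients. This is not a detail left open for an analysis plan, because the article names the tests and closes the list.

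**Working it through.** **The plan's own figure.** The inputs come from Sample size: "We selected a significance level of 0.05 and a power of 90"%, "equal allocation of participants in a 1:1 ratio between two groups and a 20% dropout rate", means of 10.65 and 9.10, and SDs of 2.08 and 1.73.

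- Difference: 10.65 − 9.10 = 1.55.
- Root-mean-square SD: √((2.08² + 1.73²)/2) = 1.913.
- Standardised effect: 1.55/1.913 = 0.81, as stated.
- n per group = 2(1.960 + 1.282)²/0.810² = 32.01, so 33 (two-sided test assumed; the article does not say).
- Dropout: 33 × 1.2 = 39.6, so 40, as stated. Dividing by 0.8 instead gives 41.25, so 42.

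The planned size therefore reproduces, and this point does not change it. With 20% dropout, 80 × 0.8 = 64 patients are evaluable, 32 per arm.

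**Type I error of the unadjusted test.** Let R² be the share of outcome variance explained by the NIHSS stratum. The documents give no value, so 5–30% is an assumption. With balanced strata the true variance of the treatment difference is (1 − R²) times what the t-test estimates. The test statistic then has SD of about √(1 − R²) under the null, and

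type I error ≈ 2[1 − Φ(1.96/√(1 − R²))].

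The table sets this beside simulated values for 32 patients in each stratum, split equally between arms.

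| R² | 1.96/√(1 − R²) | Type I error, formula | Unadjusted, simulated | Adjusted, simulated | Power, unadjusted | Power, adjusted |
|---|---|---|---|---|---|---|
| 0 | 1.960 | 0.050 | 0.050 | 0.049 | 0.89 | 0.89 |
| 5% | 2.011 | 0.044 | 0.045 | 0.051 | 0.90 | 0.91 |
| 10% | 2.066 | 0.039 | 0.039 | 0.050 | 0.90 | 0.91 |
| 20% | 2.191 | 0.028 | 0.027 | 0.048 | 0.91 | 0.94 |
| 30% | 2.343 | 0.019 | 0.017 | 0.050 | 0.93 | 0.97 |

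The power given up is about 1 point at R² of 5%, rising to about 4 at 30%, and nothing at R² of 0.

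**How much balance the allocation gives.** Ranking a list of length L and splitting it by odd and even ranks divides it exactly in half, so it acts as one large block per stratum. If m patients use it, the difference in arm counts within the stratum has variance m(L − m)/(L − 1). List lengths and an even 40 + 40 split are assumptions. For two strata of 40, the difference between arms in the share with NIHSS 0–4 has SD of about √2 × SD(count difference)/80.

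| List length per stratum, m = 40 | SD of count difference | SD of NIHSS-share difference |
|---|---|---|
| 40 (filled exactly) | 0 | 0 |
| 50 | √(40 × 10/49) = 2.86 | 5.1 points |
| 60 | √(40 × 20/59) = 3.68 | 6.5 points |
| 80 | √(40 × 40/79) = 4.50 | 8.0 points |
| Simple randomisation | √40 = 6.32 | 11.2 points |

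Even with lists of 80, the variance is about half that of simple randomisation (4.50²/6.32² = 0.51). Balance is exact only when a list is filled, and stratum sizes are not known in advance.

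**What an uncorrected imbalance would do.** If the strata differ by 2 Wexner points (assumption; range 1–3), a 10-point difference in NIHSS share moves the unadjusted estimate by 0.10 × 2 = 0.2 (0.1–0.3). That is 0.2/1.55 = 13% (6–19%) of the target difference. The standard error is 1.913 × √(2/32) = 0.48, so the shift is about 0.4 of a standard error.

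**The case against.** The strongest reply is that little is lost. Nothing in the article links NIHSS to the Wexner score. A 2-point gap between strata exceeds the SD of 1.91 and, with equal strata, implies that NIHSS explains roughly 21–27% of the variance: 1/(1 + 1.913²) = 21% if 1.913 is the within-stratum SD, or 1/1.913² = 27% if it is the total. At 5–10% the power cost is one or two points. This stands, and it sets the size of the point. It does not justify leaving the factor out, since including it costs nothing and the adjusted test keeps its level near 0.05 throughout.

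It could also be said that an analysis plan may add the covariates. But the article already fixes the tests without them and excludes supplementary analyses, so such a plan would contradict it.

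A reader might infer that the odd/even lists amount to simple randomisation and that the stratification achieves nothing. The documents do not support this. The rule is restricted randomisation, exact when a list is filled and tighter than simple randomisation otherwise. How much tighter depends on list lengths, a detail that a journal article can reasonably leave to the full protocol.

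A reader might also infer that the unadjusted result is biased. It is not: chance imbalance averages to zero over randomisations, and the test is conservative when strata are balanced.

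Finally, new envelopes in small permuted blocks might seem to follow. At a single hospital with unblinded participants and implementers and envelope allocation, small blocks make the next assignment easier to guess. That is a trade-off, not a correction of an error.

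**Conclusion.** The point holds as one about the analysis. The trial stratifies on NIHSS, but the fixed primary comparison uses neither the stratum nor the baseline score. The result is a valid but conservative test: type I error of about 0.045 down to 0.02, and about 1–4 points of power lost, for an assumed R² of 5–30% with balanced strata and 64 evaluable patients. The loss is near zero if NIHSS does not predict the Wexner score. The R² values, list lengths and stratum split are all assumptions, because the documents give none.

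On allocation, only a limited statement is supported: the scheme restrains NIHSS imbalance without guaranteeing balance, and the planned analysis would not correct what remains. The stated sample size is unaffected. The change is worth making because it is free, not because the planned test is invalid.

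**What to change.** In Statistical analyses, replace the t-test/Wilcoxon choice for the primary comparison with a linear model of the Wexner score on treatment, NIHSS stratum (0–4 or 5–15) and baseline Wexner score. The baseline value must be on the same scale as the outcome, because the Wexner system has separate constipation (0–30) and incontinence (0–20) scales. Report the adjusted difference with its 95% confidence interval. The baseline score is a further source of precision, separate from the stratification argument and not counted in the figures above.

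The cost is a change of wording. NIHSS is recorded in order to randomise, the schedule has a baseline visit, the model runs in the named software, and it fits the planned intention-to-treat analysis and multiple imputation. Make the change as a dated amendment before the treatment codes are released to the analyst. No change to the envelopes or the allocation sequence is asked for.

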### Allocation—concealment mechanism

The result of random sequences will be placed inside sealed, light-tight envelopes. These envelopes will be prepared by individuals who are not directly involved in the trial. After participants meet the inclusion criteria and provide informed consent, each of them will be given a sealed envelope to open.

## Assignment of interventions: blinding

### Who will be blinded

A third party will oversee the management and coding all data, maintaining the confidentiality of codes until the data analysis is completed. The data analyst will be blinded to the codes. The evaluation of outcomes will be performed by an assessor who is unaware to treatment allocation and has undergone training. However, it is important to note that due to the nature of bowel rehabilitation program, neither implementers of intervention nor participants can be blinded to the intervention.

### Data collection and management

Demographic and baseline information will be collected during the initial assessment. Participants will complete a well-designed questionnaire that encompasses age, sex, height, weight, types of strokes, and medication usage. The data collection will be conducted by a staff member who is not involved in the study. Data will be collected at five time points: during screening, baseline, at post-2-week intervention, at post-6-week intervention, and at 12-week follow-up. The comprehensive data collection plan is presented in Table 1. To ensure confidentiality, each participant will be assigned a unique identifier, and all collected information will be securely stored in an electronic file. Data access will be restricted until statisticians complete the data analysis at the conclusion of the study. After a period of 3 years, all data will be deleted.

**Table 1 Tab1:**
[figure not shown]
Data collection

### Additional consent provisions for collection and use of participant data and biological specimens

Participants’ stool samples will be collected to assess fecal characteristics using the BSFS. Each participant will be provided with a disposable EasySampler collection kit for stool collection. The collected stool samples will be stored within a temperature range of 10 °C to 25 °C. The analysis of stool samples will involve a visual comparison to the BSFS, allowing for the determination of stool consistency and type. Upon completion of the assessment, typically within 24 h, the stool samples will be promptly and securely destroyed. Informed consent will be obtained prior to collecting these samples. Participants will be informed that any personal information collected during the study will be encoded and kept strict confidentiality. Furthermore, there are no intentions to conduct ancillary studies utilizing the data generated from this trial.

### Plans to promote participant retention and complete follow-up

To facilitate follow-up, participants will receive a bowel intervention diary and on-site observations. To encourage participants’ active involvement in the study, they will be informed the benefits and offered compensation for completing assessments. Regular phone reminders will be sent during the follow-up period.

### Statistical analyses

The collected data will undergo analysis using IBM SPSS Statistics 25.0 (IBM Corp., Armonk, NY, USA). Baseline characteristics will be summarized using descriptive statistics. Continuous variables, such as the Wexner score and quality of life score, will be reported using means, medians, standard deviations, and score ranges. Categorical valuable, such as BSFS, will be reported as counts and percentages. To ascertain normality, the Kolmogorov-Smirnova test will be applied. In instances of normally distributed data, independent samples *t*-test will be employed to compare efficacy between the intervention and control groups in terms of the Wexner score, PAC-QoL, and FI-QoL. Non-normally distributed data will be analyzed using the Wilcoxon rank sum test with a test statistic of *Z*. For assessing changes across distinct time points, we will employ repeated measures ANOVA. The chi-squared test will be used to analyze categorical data for the BSFS. A *p*-value < 0.05 will be considered statistically significant. We will perform an intention to treat analysis for participants who either lack adherence to bowel care (defined as comply with less than 80% of bowel care) or discontinue the study. These participants will be retained within their originally randomized treatment arm for analysis. Addressing missing data, a multiple imputation method will be implemented. No supplementary analyses will be carried out in this study, and the study design does not encompass interim analyses.

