## Methods/design

### Study design

This study is a single-blind, prospective, randomized controlled, parallel-group superiority trial designed to compare the effectiveness of a rehabilitation program that combines DRS with abdominal massage against the standard care provided to stroke patients with NBD.  This trial protocol uses the Standard Protocol Items: Recommendations for Interventional Trials (SPIRIT) reporting guidelines (see Additional file 1). 

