## Outcomes

### Primary outcome

The primary outcome in this trial is Wexner score, a widely recognized assessment tool extensively employed in clinical practice to assess bowel dysfunction [21]. The Wexner score encompasses both constipation and fecal incontinence scales. The constipation scale comprises 8 items: frequency of defecation, difficulty, completeness, pain assessment, duration of defecation (in minutes), assisted defecation, number of unsuccessful defecations attempts per 24 h, and duration of constipation (in years). The rating of assisted defecation follows a scale of 0–2, while the other items are graded on a scale of 0–4, representing a range from mild to severe [22]. The overall score ranges from 0 to 30, with higher scores indicating greater severity of constipation symptoms.

The Wexner incontinence scale assesses the frequency of gas, liquid, and solid incontinence, in addition to the utilization of pads and lifestyle adjustments [23]. The total score ranges from 0 to 20, with higher scores correlating to increased severity. Item scores vary from 0 to 4, where 0 signifies “never” and 4 signifies “always.” A score of 1 signifies occasional incontinence, while a score of 2 denotes “sometimes,” and a score of 3 indicates “often.”

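### The primary Wexner comparison is a valid but unadjusted t-test or Wilcoxon test, chosen by a normality pre-test; it leaves out baseline score and NIHSS stratum and so gives up precision and a fixed effect measure

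*Protocol article*

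**What the plan says.** All references are to the protocol article.

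- **Statistical analyses.** The choice of test rests on a pre-test: "To ascertain normality, the Kolmogorov-Smirnova test will be applied". If the data pass, the independent-samples t-test "will be employed to compare efficacy between the intervention and control groups in terms of the Wexner score, PAC-QoL, and FI-QoL". If they fail, the Wilcoxon rank sum test is used. No covariate is named for either test. Repeated measures ANOVA is planned for change over time, also without a covariate or stratum, and it is not called the primary comparison. The section ends by ruling out supplementary and interim analyses.
- **Allocation—sequence generation.** "Participants will first be stratified into two groups based on their baseline National Institutes of Health Stroke Scale (NIHSS) scores", with strata 0–4 and 5–15. Within each stratum, ranked random numbers alternate between the arms, so the arms are close to balanced by stratum.
- **Data collection and management.** There is a baseline visit, then assessments at 2 weeks, 6 weeks and the 12-week follow-up. Collection of the Wexner score at baseline is inferred from this, because the data collection table is not shown.
- **Sample size.** The trial is sized on means of 10.65 and 9.10 and SDs of 2.08 and 1.73, at 90% power with 20% dropout, giving 40 per group.

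**The concern.** The protocol itself fixes these tests and closes the door on other analyses, so this is not a detail left open for an analysis plan. Two pieces of information that the trial holds, or should hold, before treatment starts are not used in the between-arm comparison.

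- **Baseline score.** A symptom score after treatment usually correlates with the same score before it. Conditioning on baseline narrows the confidence interval and corrects chance imbalance, which matters with about 32 evaluable patients per arm.
- **NIHSS stratum.** Stratified randomisation removes between-stratum variation from the treatment contrast. An analysis that ignores the stratum leaves that variation in the standard error, so the test is somewhat conservative.
- **Choice of test.** A mean difference and a rank shift answer different questions. With the pre-test, the data decide which one the trial reports as its primary result.

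**Working it through.** **Inputs.** Difference 10.65 − 9.10 = 1.55; SDs 2.08 and 1.73; α = 0.05; power 90%; dropout 20% (Sample size). Sidedness is not stated; two-sided is taken, as the design is a "parallel-group superiority trial designed to compare the effectiveness". The baseline-outcome correlation ρ is not in the document and is assumed to lie between 0.3 and 0.7.

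**1. Reproduce the plan's figure.**
- Pooled SD = √((2.08² + 1.73²)/2) = √3.660 = 1.913.
- Effect size = 1.55/1.913 = 0.81, as stated.
- Two-sided normal formula: n = 2 × (1.960 + 1.282)² / 0.810² = 32.01 per arm, and 32/0.8 = 40.

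The stated 40 therefore corresponds to an unadjusted two-group comparison. (Rounding up to 33 gives 42 after dropout. The noncentral t needs 34 evaluable, or 43 after dropout. A one-sided test gives 27 and 34, which does not match.)

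**2. Precision with baseline adjustment.** ANCOVA multiplies the residual variance by 1 − ρ². With 32 per arm, SE = 1.913 × √(1 − ρ²) × √(2/32), and the noncentrality is 1.55/SE. Degrees of freedom are 62 unadjusted, and 60 with baseline and stratum in the model.

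| Analysis | Variance factor | SE (points) | Noncentrality | Power at 32/arm | Evaluable n/arm for 90% |
|---|---|---|---|---|---|
| Unadjusted t-test | 1.00 | 0.478 | 3.24 | 89.1% | 34 |
| ANCOVA, ρ = 0.3 | 0.91 | 0.456 | 3.40 | 91.7% | 31 |
| ANCOVA, ρ = 0.5 | 0.75 | 0.414 | 3.74 | 95.7% | 26 |
| ANCOVA, ρ = 0.7 | 0.51 | 0.342 | 4.54 | 99.4% | 18 |

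These figures take all 32 patients per arm as contributing to the scale analysed, as the plan's own calculation does.

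**3. Cost of omitting the stratum.** If the stratum explains a share R² of outcome variance and the arms are balanced within strata, the true two-sided α of the unadjusted test is 2 × (1 − Φ(1.960/√(1 − R²))). For assumed R² of 2%, 5% and 10% this gives 0.048, 0.044 and 0.039. The test is conservative, and mildly so.

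**4. What the normality gate does.** Simulation with 32 per arm, 4,000 runs, a Lilliefors-type Kolmogorov-Smirnov test in each arm (assumed, as the protocol does not say which form or to what it is applied), SD 1.913 and a shift of 1.55:

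| Score distribution | Sent to Wilcoxon | Type I error, gated | Power, gated | Power, always t-test |
|---|---|---|---|---|
| Normal, continuous | 9–10% | 0.049 | 88.9% | 89.1% |
| Normal, rounded to integers | 79–80% | 0.052 | 85.5% | 88.0% |
| Exponential | about 97% | 0.045 | 97.7% | 88.1% |

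Type I error stays near 5% throughout. The gate costs about 2.5 points of power for rounded normal scores and helps under strong skewness. It does not fix the effect measure: rounding alone sends about four trials in five to the rank test.

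**The case against.** An unadjusted comparison of randomised arms is unbiased, it is what the trial was sized for, and the simulated type I error is near nominal. All of this stands. The protocol contains no invalid inference on this point, and the case is one of efficiency and pre-specification.

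The repeated measures ANOVA might be said to use the baseline data already. If baseline is one of its time levels, it does so in part. But the protocol does not tie it to the primary comparison, and it omits the stratum.

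The text does not say whether the t-test is on the follow-up score or on change from baseline. If it is on change, baseline is used, though less efficiently. With equal variances, the change-score variance factor is 2(1 − ρ), that is 1.4, 1.0 and 0.6 for ρ = 0.3, 0.5 and 0.7, against 0.91, 0.75 and 0.51 for ANCOVA.

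A reader might infer more than the document supports:

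- **That the Kolmogorov-Smirnov gate cannot detect skewness.** This depends on its form. For samples of 32 from a clearly skewed gamma distribution (shape 2), the plain test rejects in about 3% and the Lilliefors form in about 48%. The form is not stated.
- **That "duration of constipation (in years") adds pure noise to the outcome.** This would apply only if follow-up rather than change scores are compared, and only on the constipation scale. Its share of the variance cannot be computed from the document.
- **That a Wilcoxon result leaves no estimate in Wexner points.** The protocol reports means, medians and SDs for the scores in any case, and a Hodges-Lehmann shift with an interval can accompany the rank test.
- **That power is far lower because only part of each arm contributes to each Wexner scale.** The document gives no split between constipation and incontinence, so no such figure can be fixed.

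**Conclusion.** The point holds as a recommended improvement. The planned primary test is valid but gives up precision, is slightly conservative after stratified randomisation, and leaves the choice between a mean difference and a rank shift to the data.

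The gain from adjustment runs from under 3 points of power (89% to 92%, ρ = 0.3) to about 10 points (89% to 99%, ρ = 0.7). Three things limit how firmly this can be stated: ρ is assumed, baseline Wexner collection is inferred, and 32 evaluable patients per arm are taken to contribute to one scale. The direction does not depend on where ρ falls in this range.

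It should not be read as inflation of type I error, nor as a finding that the trial is too small. Neither the protocol's figures nor the simulations show that.

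**What to change.** In the statistical section, name one primary analysis:

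- an ANCOVA of the Wexner score at one named time point on treatment. The end of the 6-week intervention is a natural example, but the protocol names no primary time point, so the investigators must state it;
- covariates: the baseline score on the same scale and the NIHSS stratum (0–4 / 5–15);
- a separate model for the constipation scale and the incontinence scale. Their ranges are 0–30 and 0–20, and a covariate for symptom type in one pooled model would not make them commensurable;
- the adjusted difference with its 95% CI as the reported result.

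Use the same model for PAC-QoL and FI-QoL. Delete the Kolmogorov-Smirnov gate. If residuals are clearly non-normal, use robust or bootstrap standard errors, and keep the Wilcoxon test as a sensitivity analysis. The sentence excluding supplementary analyses needs a matching edit.

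The cost is protocol or analysis-plan wording, settled before treatment codes are released to the analyst. It needs no extra patients or visits. The stratum is already recorded, the baseline score should be, and the named software fits the model. Confirm against the data collection table that both Wexner scales and both quality-of-life instruments are recorded at baseline.

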### Eligibility criteria

To be eligible for participation in this study, individuals must meet the following criteria: (1) age ≥ 18 years old, (2) stable phase stroke (no stroke relapses within the past 3 months), (3) awake consciousness and stable vital signs, (4) NIHSS score ≤ 15, and (5) bowel dysfunction according to the criteria of Rome IV:Constipation is defined as meeting any 2 of the following features:Difficulty with stool passage in 25% or more of bowel movements,Hard stool or lumpy consistency (Bristol Stool Form Scale type 1–2 stool) in 25% or more of bowel movements,Incomplete evacuation in 25% or more of bowel movements,Obstruction or blockage sensation in 25% or more of bowel movements,Need for digital help with 25% or more of bowel movements,Spontaneous bowel movements less than 3 times per week.Rare loose stools without the use of laxatives.Not meeting the criteria for irritable bowel syndrome.

*The symptoms of constipation must have been present for a minimum of 6 months prior to diagnosis and persisted for the preceding 3 months, in accordance with the aforementioned criteria. It is important to exclude opioid-induced constipation.

Fecal incontinence is defined as recurrent instances of uncontrolled fecal excretion.

*Patients must have experienced symptoms of fecal incontinence for a minimum duration of 6 months prior to diagnosis, with occurrences ranging from 2 to 4 times within the past week.

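### The chi-squared test for the Bristol stool scale has no stated grouping or direction, so it is inefficient and does not ask whether more stools became normal

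*Protocol article*

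**What the plan says.** The section on the Bristol Stool Form Scale describes "a standardized scale that classifies stool consistency into seven categories". It then gives the types a meaning: "Types I and II signify constipation; whereas types III and IV are regarded as the optimal stool shapes", and at the other end "Types V to VII indicate the potential for diarrhea". The good result therefore lies in the middle of the scale, with abnormal types on both sides.

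The Eligibility criteria admit two kinds of patient. For one, "Constipation is defined as meeting any 2 of the following features"; for the other, "Fecal incontinence is defined as recurrent instances of uncontrolled fecal excretion". The Skin care section has rules for Bristol scores of 5, 6 and 7, so loose stools are expected in some participants.

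Under Statistical analyses, the scale is treated as categorical: "Categorical valuable, such as BSFS, will be reported as counts and percentages". The comparison between arms is then fixed: "The chi-squared test will be used to analyze categorical data for the BSFS". No grouping of types, direction of benefit or split by symptom type is given. The section also rules out supplementary analyses and plans an intention-to-treat analysis with multiple imputation. Randomization is stratified by NIHSS score (0–4 and 5–15), not by symptom type.

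**The concern.** A chi-squared test across the types asks whether the two distributions differ in any way. The trial is declared a superiority trial, and the relevant BSFS question is whether more patients reach a normal stool. A constipated patient improves by moving up the scale, and a patient with loose stools by moving down. The stated test cannot tell either change from a shift between one abnormal end and the other.

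Two things are at stake. A real gain in normal stools may be missed because the evidence is spread over six degrees of freedom. And a significant p-value may arise with no gain in normal stools at all. Because supplementary analyses are ruled out, the article as written leaves no room for a normal-versus-abnormal comparison later.

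**Working it through.** **Sample sizes.** The protocol gives no power figure for the BSFS, so the only figure to reproduce is the Wexner sample size. Its inputs are a difference of 10.65 − 9.10 = 1.55, SDs of 2.08 and 1.73, α of 0.05 (two-sided assumed) and 90% power.
- Pooled variance = (2.08² + 1.73²)/2 = 3.660, so the SD is 1.913.
- n = 2 × (1.960 + 1.282)² × 3.660 / 1.55² ≈ 32.0 per arm, and 32.0/0.8 = 40.

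The stated 40 per group is reproduced. The planned intention-to-treat set with imputation is 40 per arm; 32 per arm is the set of completers at 20% dropout.

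**Sparsity.** A 2×7 table has 14 cells. The average expected count is 80/14 = 5.7 at 40 per arm and 64/14 = 4.6 at 32 per arm.

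**Assumed BSFS distributions (types I to VII).** These are illustrations, because the protocol gives no rates.
- Control: .20, .20, .12, .18, .10, .10, .10 (30% optimal).
- Intervention A: .09, .10, .27, .36, .06, .06, .06 (63% optimal).
- Intervention B: .12, .13, .22, .28, .09, .08, .08 (50% optimal).

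**Why power falls.** With n per arm and category probabilities a and b, the chi-squared noncentrality is λ = n × Σ(a − b)²/(a + b). For scenario A at n = 40:
- Seven types: 40 × 0.2227 = 8.91 on 6 df (critical value 12.59), power 58%.
- Three bands (.40/.30/.30 versus .19/.63/.18): 40 × 0.2218 = 8.87 on 2 df (critical value 5.99), power 76%.
- III–IV versus other: 40 × (0.33²/0.93 + 0.33²/1.07) = 40 × 0.2189 = 8.75 on 1 df (critical value 3.84), power 84%.

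The signal is almost the same in all three tests; only the degrees of freedom differ. Simulated tables (20,000 or more per scenario) give similar power:

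| Scenario | n per arm | 2×7 | Three bands | III–IV vs other |
|---|---|---|---|---|
| 30% vs 63% | 40 | 59% | 79% | 87% |
| 30% vs 63% | 32 | 47% | 68% | 79% |
| 30% vs 50% | 40 | 24% | 38% | 46% |
| 30% vs 50% | 32 | 19% | 31% | 40% |

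The average share of 2×7 cells with expected count below 5 is 40–46% at 40 per arm and 57–59% at 32 per arm. With three bands it is about 1% or less. With equal distributions, the 2×7 test rejects in about 4–4.5% of trials.

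**Does a rejection mean improvement?** Keep 30% optimal in both arms and move 30 points from hard to loose: types I–II go from 40% to 10%, and V–VII from 30% to 60%. At 40 per arm the 2×7 test rejects in about 71% of trials and the three-band test in about 89%. At 32 per arm the figures are about 58% and 80%. The III–IV comparison stays at 5%.

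**Would a rank test on types 1–7 do instead?** No. When gains came from both ends in the same proportions, its power was about 5–17% even for a 30-point gain in normal stools, because the two movements cancel.

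**The case against.** The strongest objection is that the article never says all seven types enter the table separately. Its only interpretation of the scale uses three bands, and grouping is the kind of detail a fuller document may settle. Under that reading sparsity almost vanishes and much of the power returns. This stands as a limit on the size of the point: 2×7 is the natural reading, not an explicit one. It does not remove the point, because the three-band test is equally directionless.

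A reader might infer several stronger charges that the documents do not support.
- *The test is invalid, or mixing symptom types biases it.* Its type I error is sound. Opposite movements do not bias a chi-squared test; they only leave a rejection without a meaning.
- *Expected counts average below 5.* That holds at 32 per arm (4.6) but not for the planned set of 40 (5.7).
- *Most of the power is wasted.* In the larger scenario about two thirds survives at 40 per arm (59 of 87 points), and in the smaller one about half (24 of 46).
- *The fault is ignoring the order of the types.* Ignoring order is defensible here, given how a rank test performs.

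It is also fair that the counts and percentages let a reader see direction beside the p-value, that the assumed gains fall in types III–IV and so favour a test aimed there, and that the III–IV comparison cannot see hard-to-loose shifts. In one run, moving 20 points from I–II to V–VII at 32 per arm gave 5% rejection for III–IV versus other and 39% for three bands.

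**Conclusion.** The point holds as one of efficiency and interpretation in a secondary outcome. The chi-squared test is valid, but without grouping or direction it does not test what the protocol itself calls a good result: "types III and IV are regarded as the optimal stool shapes".

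Read as 2×7 at 40 per arm, it gives up about 28 percentage points of power in the larger assumed scenario (59% against 87%) and about 22 in the smaller (24% against 46%). With three bands the loss shrinks to about 8 points in each (79% against 87%, and 38% against 46%), but a 30-point hard-to-loose shift with no gain in normal stools would still be declared significant in most trials.

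The exact losses rest on assumed BSFS rates. The ranking of the tests held in every scenario examined that had a gain in normal stools. How many patients start at each end is unknown, since incontinence is not defined by loose stool. The Wexner conclusion and the 40 per group are not affected.

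**What to change.** Define the BSFS endpoint as the proportion of participants in types III–IV at the end of the 6-week intervention. Compare the arms by a risk difference with a 95% CI, Mantel-Haenszel stratified by the NIHSS randomization stratum. Alternatively, use logistic regression with NIHSS stratum and baseline symptom type as main-effect covariates. Do not cross the two factors: four strata would leave about 10 per arm in each (8 among completers) even if evenly filled. State how patients with both constipation and incontinence are classified. Show the full seven-type distribution descriptively, by arm and symptom type.

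The cost is a change of wording, made before unblinding so that the grouping is not chosen from the data. It needs no new visits, measurements or sample size. The downside is that shifts between abnormal types, such as hard to loose, would appear only in the descriptive table.
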